## Abstract

**Objectives:**

To conduct mental health surveillance in adults in Ukraine and Ukrainian refugees (Canton of Zurich, Switzerland) as an actionable scientific foundation for public mental health and mental healthcare.

**Methods:**

Mental Health Assessment of the Population (MAP) is a research program including prospective, population-based, digital cohort studies focused on mental health monitoring. The study aims to include 17,400 people from the general population of Ukraine, 1,220 Ukrainians with refugee status S residing in the canton of Zurich, and 1,740 people from the Zurich general population. The primary endpoints are prevalence and incidence of symptoms of: posttraumatic stress disorder (measured by PCL-5), depression (PHQ-9), anxiety (GAD-7), and alcohol use disorder (AUDIT). Secondary endpoints include participants’ health-related quality of life (EQ-5D-5L and EQ-VAS), experiences of somatic distress syndrome (PHQ-15), social isolation, social integration, and mental wellbeing (SWEMWBS).

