**FIGURE 1 F1:**
[figure not shown]
Mental Health Assessment of the Population, Ukraine 2024. Note. ^1^ in accordance with the Resolution of the Cabinet of Ministers of Ukraine dated October 14, 2022, No. 1159 “On approval of the Procedure for the development, holding of public discussion, approval of programs for the comprehensive restoration of the region, the territory of the territorial community (its parts), and making changes to them.” Access mode: https://zakon.rada.gov.ua/laws/show/1159-2022-%D0%BF#Text). Date of assessment: 15 June 2024.

Because of the unstable situation in specific oblasts, we decided not to focus on individual oblasts for the analyses but on regional clusters of oblasts, defined by i) level of proximity to the hostilities zone/border with the aggressor = country-aggressor Russian Federation ii) consequences of the full-scale Russian invasion - level of destruction and loss of life; iii) geographical factors.

Cluster North-West (Rivne, Lviv, Chernivtsi oblasts): North-western Ukraine. These oblasts are remote from the hostilities zone and have low security risks due to their proximity to the EU border. There were no direct hostilities in these territories; therewas no large-scale destruction of infrastructure or housing due to hostilities; there has been significant population movement to this region.

Cluster Central (Zhytomyr, Kyiv, Dnipropetrovsk oblasts): Central Ukraine. These oblasts are far from the border with the aggressor and have medium security risks. Part of the territory experienced hostilities in the first months of the full-scale invasion; some areas were temporarily occupied or surrounded; there was destruction of infrastructure and housing due to hostilities and/or shelling.

Cluster South-East (Sumy, Kharkiv, Mykolaiv, Kherson oblasts): South-eastern Ukraine. These oblasts are close to the hostilities zone and have high security risks due to their proximity to the border with the aggressor. Most of the territory experienced hostilities, which are currently ongoing; a large part of the territory was temporarily occupied, and some settlements remain under occupation; significant destruction of infrastructure and housing stock due to hostilities and/or shelling is present; there has been mass emigration of the population to other regions and/or countries and a sharp deterioration in the level of socio-economic development.

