#### Sample Size Considerations and Calculation

We expect a prevalence of 15% for alcohol use disorder, 25% for anxiety and depression and 40% for PTSD in the Ukrainian population based on the available prevalence data in Ukraine and on data from other conflict areas [11]. Sample size requirements are highest for a prevalence of 40%, on which we thus base sample size calculations. We consider a specific age group in a specific cluster (e.g., participants 25–44-year-old in a specific cluster of oblasts) as the unit for which we need a certain precision to estimate prevalence. To provide a precision of ±5% in estimating prevalence with 95% confidence intervals for a specific age group in a specific cluster, the required sample size is 369 survey respondents per combination of age group and cluster. Assuming a potential attrition of 15% among those who consent to participate, the required sample size for enrolment is 435 per age and cluster stratum. The size of the target sample is 5,220 persons (net sample; given 4 age and 3 cluster of oblasts strata). Considering a participation rate of approximately 7% for MAP-U, reflecting the difficult situation in Ukraine, the final number to be randomly drawn from the population registry in Ukraine is 1,740 per stratum and 74,570 for the total sample, respectively. For the MAP-Z study, a participation rate of 25% is assumed based on experiences with previous population-based studies in the canton of Zurich (e.g., Corona Immunitas studies). For the age groups of 25–44 and 45–64 years in people living with protection status S as well as for all four age groups of the general population of the canton of Zurich we will also have 435 participants per age group, or 1,740 people to be invited initially. But there are less than 1,740 people with protection status S in the youngest (18–24 years) and oldest (65+ years) age group with protection status S in Zurich. Thus, we will aim for randomly selecting 684 people in those two age groups in order to have 171 (25%) finally included. In these age groups, the precision will be lower, and 95% CI expected at ±8%. The total sample sizes for people living with protection status S and for the general population living in the canton of Zurich will thus be 1220 and 1740, respectively.

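### The Abstract gives a MAP-U inclusion target of 17,400, but the sample size section derives a net target of 5,220, and nothing reconciles the two

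*Protocol article*

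**What the plan says.** The Methods paragraph of the Abstract gives three recruitment targets. For MAP-U it says "The study aims to include 17,400 people from the general population of Ukraine". For Zurich it gives 1,220 people with status S and 1,740 from the general population.

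The section Sample Size Considerations and Calculation builds the MAP-U number step by step:

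- Design prevalence: "Sample size requirements are highest for a prevalence of 40%, on which we thus base sample size calculations".
- Precision: "To provide a precision of ±5% in estimating prevalence with 95% confidence intervals for a specific age group in a specific cluster", for which "the required sample size is 369 survey respondents per combination of age group and cluster".
- Loss after consent: "Assuming a potential attrition of 15% among those who consent to participate", "the required sample size for enrolment is 435 per age and cluster stratum".
- Total: "The size of the target sample is 5,220 persons (net sample; given 4 age and 3 cluster of oblasts strata").
- Number drawn: at about 7% participation, 74,570 in total. The same sentence gives 1,740 for each stratum.

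The section ends by stating a precision of ±6% to 7% when results are also split by sex.

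The three-cluster structure is explained in the MAP-U part of the population section. Ten oblasts are sampled, but the authors say "we decided not to focus on individual oblasts for the analyses but on regional clusters of oblasts".

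**The concern.** The article gives two numbers for how many people MAP-U will include, and the larger is more than three times the smaller. The Abstract is the most widely read part of the article, and readers will judge recruitment against its figure. If MAP-U enrols exactly what the sample size section plans, it will appear to have reached 5,220/17,400 = 30% of its target. If the field team recruits to the Abstract figure, it needs far more invitations than the plan provides for. A reader cannot tell from the article which target is current.

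**Working it through.** **Inputs** (all from Sample Size Considerations and Calculation unless noted): prevalence p = 0.40; half-width d = 0.05; 95% confidence, z = 1.96; attrition 15%; 4 age groups x 3 clusters = 12 strata; participation about 7%. The 10 oblasts come from the MAP-U population section, and 17,400 from the Abstract.

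**Step 1. Reproduce the plan's own figure.**

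- Respondents per stratum: n = z² p(1 − p)/d² = 1.96² x 0.40 x 0.60/0.05² = 368.8, rounded up to 369. Stated: 369.
- Enrolled per stratum: 369/(1 − 0.15) = 434.1, rounded up to 435. Stated: 435.
- Net MAP-U sample: 435 x 12 = 5,220. Stated: 5,220.
- Number drawn: 5,220/0.07 = 74,571. Stated: 74,570.

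**Step 2. Check the stated precision against 5,220.** Half-width = 1.96 x √(0.40 x 0.60/n).

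| Unit | n | Half-width | Stated |
|---|---|---|---|
| Stratum, after attrition | 369 | ±5.0% | ±5% |
| Stratum split equally by sex, before attrition | 435/2 = 217.5 | ±6.5% | ±6% to 7% |
| Stratum split equally by sex, after attrition | 369/2 = 184.5 | ±7.1% | ±6% to 7% |

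Both stated precisions go with 5,220.

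**Step 3. Try to obtain 17,400.**

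- As the number drawn: the plan gives 74,570. The stray 1,740 for each stratum gives 1,740 x 12 = 20,880. Neither is 17,400.
- As a different kind of count: the other two figures in the same Abstract sentence, 1,220 and 1,740, are the total sample sizes stated for Zurich, that is, people included. The MAP-U figure has to be read the same way.
- As a product of plan quantities: 435 x 4 x 10 = 17,400 exactly, with 10 being the number of oblasts. The ratio 17,400/5,220 = 3.33 is 10 oblasts over 3 clusters. The current derivation does not use this product.

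**Step 4. What 17,400 would mean under the current strata.**

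- Enrolled per stratum: 17,400/12 = 1,450, or 1,450 x 0.85 = 1,232.5 after attrition.
- Half-width: ±2.5% (n = 1,450) or ±2.7% (n = 1,232.5), against ±5% planned.
- Number drawn: 17,400/0.07 = 248,571, against 74,570 planned.

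**Step 5. The per-stratum number drawn.** At 7% participation, 435/0.07 = 6,214, and 74,570/12 = 6,214. The stated 1,740 for each MAP-U stratum fits neither. It equals 435/0.25, which uses the participation rate assumed for MAP-Z.

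**The case against.** The best defence is that the Methods section carries a complete and correct derivation. The figures 369, 435, 5,220 and 74,570 all reproduce, and no endpoint, model, stratum or stated precision depends on 17,400. On this view the slip is editorial and confined to the Abstract. It stands that the calculation leading to 5,220 is sound and that the analysis plan is unaffected. That does not remove the conflict, because a publicly stated enrolment target is relied on in its own right.

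Two readings that would reconcile the numbers fail. 17,400 is not the number invited, for the reasons in Step 3. Nor is 5,220 only a minimum for precision, since the section presents it as the net target sample.

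A reader might also infer more than the article supports:

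- **That the stated precisions contradict each other.** They do not. The Abstract gives no precision, and both statements in the sample size section agree with 5,220. The ±2.5% to 2.7% in Step 4 is only what 17,400 would imply.
- **That the Abstract promises oblast-level precision, or that 17,400 is known to come from an abandoned oblast-level design.** The exact product and the decision to analyse clusters make a leftover figure plausible. However, the Abstract sentence mentions neither oblasts nor strata, and nothing in the article gives the origin of the number.
- **That age-by-oblast cells would be too small.** The plan does not analyse such cells, so their size is no test of it.

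**Conclusion.** The contradiction holds. The article states two net inclusion targets for MAP-U, 17,400 and 5,220, a factor of 3.33 apart, and no text reconciles them. The stated inputs and both stated precisions support 5,220. The conclusion rests on reading the Abstract figure as people included, which its wording and the two Zurich figures beside it both require. The precision check for the split by sex assumes equal numbers of women and men. The full protocol is not shown, so which target the investigators now hold is for them to confirm. A headline sample size more than three times what the described design plans to enrol should be corrected, even though no calculation or analysis depends on it.

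**What to change.** State one MAP-U target in both places.

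- **If the three-cluster design is current:** change the Abstract figure to 5,220. This corrects one number; the headline becomes smaller and nothing in the design changes.
- **If 17,400 is still intended:** restate the strata, the number drawn and the precision in Sample Size Considerations and Calculation so that they lead to it. At 7% participation that means about 248,571 people drawn, so this is a change of design and resources, not of wording.

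In the same edit, correct the 1,740 to be drawn in each MAP-U stratum. With 435 enrolled and 7% participation the figure is about 6,214, which is also what the 74,570 total implies over 12 strata.

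The registry entry was not available for this review. It should be checked for consistency with the corrected number, and no error in it is alleged.

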**Results:**

Baseline assessment starts in March 2024 with follow-ups occurring every 3 months for at least 2 years.

**Conclusion:**

MAP will generate reliable, comparable, and high-quality epidemiological data to inform public mental health and healthcare policies in the Ukrainian population.

**ISRCTN Registry:**

https://www.isrctn.com/ISRCTN17240415.

## Introduction

Mental health challenges are pervasive and long-lasting in post-war societies, often associated with intra-familial violence or substance abuse [1]. Even before the Russian invasion in 2022, Ukraine already had a high mental health burden. Some of the drivers for this burden include historical Soviet-era trauma, Russia’s invasion of Ukraine in 2014, and, more recently, COVID-19 [2, 3].

Prior to the war, the prevalence of most mental health conditions in Ukraine was similar to those in Eastern Europe. However, the prevalence of alcohol use disorders was notably higher in Ukraine (6.0%) compared to the global average (1.5%) [4]. The current, unmeasured, public mental health crisis in Ukraine likely began before the start of the war with the Russian occupation in 2014. A study from 2016 on mental health of internally displaced persons in Ukraine (due to the armed conflict in the east of Ukraine) estimated a prevalence of 32% for posttraumatic stress disorder (PTSD), 22% for depression, and 17% for anxiety [5], which is several times higher than the Eastern European average. A further analysis found that 55% of respondents were at risk for developing a somatic symptom disorder [6] and 8.4% of men as well as 0.7% of women tested positive for alcohol use disorder [7].

According to WHO global estimates, one in five people living in an area affected by conflict at any time during the previous 10-year period is estimated to have some form of mental health condition, ranging from mild depression or anxiety to even psychosis. Almost one in 10 is expected to live with a moderate or severe mental health condition [8]. Applying these estimates to the population of Ukraine (about 43.7 million) [9], approximately 9.6 million people may live with a mild mental health condition and 3.9 million with a moderate or severe mental health condition. In addition to these projections that reach the diagnostic criteria of mental health conditions, an even larger proportion of the population is likely to experience distress, with common presentations such as feelings of anxiety and sadness, hopelessness, difficulty sleeping, fatigue, irritability, or anger [10].

While the long-term, population-level mental health impact of Russia’s invasion of Ukraine since 24 February 2022, cannot yet be fully predicted, increased demand for mental health and psychosocial support is anticipated both during the ongoing war and in a post-war context. Mental wellbeing of the Ukrainian population is key for societal and economic recovery and for long-term development. Some early work has assessed some mental health outcomes cross-sectionally [11–13] but no ongoing longitudinal mental health surveillance program in Ukraine is in place. Consequently, neither the public nor health authorities are informed in a timely manner about mental health needs of the population or the consequences of war activities on mental health conditions and health behaviours. Furthermore, mental health support, care needs, and acceptance are likely to vary across subgroups, for example, depending on the level of exposure to front-line violence (i.e., place of residence), and across vulnerable populations. Mental health surveillance programs to determine population and subgroup level mental health needs are essential to inform planning and allocation of services by the Ukrainian healthcare system, development partners, and both national and international organizations, including the International Committee of the Red Cross (ICRC). In the mid- and long-term, it is important to monitor the temporal development of mental health of the Ukrainian population and especially vulnerable subgroups to efficiently allocate resources for the large, expected need for community and mental healthcare.

Here, we describe the protocol of Mental Health Assessment of the Population (MAP), a research program consisting of longitudinal studies on mental health monitoring of the Ukrainian population. These studies are conducted across different regions in Ukraine and in the Canton of Zurich, Switzerland. The aim is to generate reliable data to inform public mental health and healthcare planning and evaluation.

### Study Objectives

The main goal of the MAP program is to implement an agile, digital surveillance of public mental health in adult people living in different parts of Ukraine and in Ukrainian refugees living in the Canton of Zurich, Switzerland. The specific objectives are: (1) to determine the prevalence of symptoms of PTSD, depression, anxiety, and alcohol use disorder (a) at the beginning of the surveillance, and (b) up to at least 2 years; (2) to determine short-term and long-term temporal developments of mental health in the Ukrainian general population (in Ukraine and in the Canton of Zurich) and subgroups defined by age and level of war-related exposure; (3) to assess how mental health impacts general health and healthcare seeking behaviour; and (4) to assess needs, preferences, barriers, and facilitators for mental healthcare services of the Ukrainian general population and subgroups.

## Methods

The protocol has been developed by an interdisciplinary and international team of Ukrainian and Swiss scientists, supported by stakeholders from universities and organizations in both countries. These include members of the ICRC, representatives from the University Hospital of Psychiatry Zurich, the Paediatrics Children’s Hospital of Zurich, and public health officials from Ukraine and Switzerland. It also involves experts in public and mental health, political science, health policy, and representatives from governmental (Ukrainian and Swiss) and non-governmental organizations (e.g., ICRC, UNESCO), as well as social media specialists.

### Study Design

The overarching MAP research program includes two related prospective, population-based, digital cohort studies: the Mental Health Assessment of the Population in Ukraine (MAP-U), which focuses on adult people living in Ukraine, and the Mental Health Assessment of the population in Zurich (MAP-Z), focusing on forcibly displaced Ukrainian citizens (refugee status S) living in the Canton of Zurich in Switzerland. MAP-Z also includes a control group of people from the general population of the Canton of Zurich not directly affected by the war. To maximize comparability between MAP-U and MAP-Z, we will use the same mental health surveillance protocol.

The project is conducted by the Epidemiology, Biostatistics and Prevention Institute (EBPI), University of Zurich (UZH), and Sumy State University, whereas the Embassy of Ukraine in Switzerland, Ministry of Health Ukraine, Center for Public Health Ukraine, as well as the Swiss partners Mental Health for Ukraine (MH4U) and the Swiss Agency for Development and Cooperation are cooperation partners.

The protocol has been approved by the responsible ethics committee of the canton of Zurich, Switzerland (Kantonale Ethik-Kommission Zürich; BASEC-Nr. 2023-02247) and by the Commission on Bioethics of Sumy State University, Ukraine (ref-Nr. 60-0274). The protocol has been prospectively registered on the International Standard Randomised Controlled Trial Number (ISRCTN17240415).

Upon enrolment, participants will complete the baseline assessment through a secure digital study platform (REDCap) [14, 15]. To access REDCap for the baseline and follow-up assessments, randomly selected persons in Ukraine will receive an email (automated, including reminders) containing a link to the respective assessment. If there is no response, we will approach them via Telegram or phone calls. For MAP-Z, the initial contact will be established by postal mail which has been proven to be a successful way in other population-based studies. Follow-up assessments, where participants will be invited by email or Telegram, will take place every 3 months for at least 2 years. The study design thus follows that of the digital cohort of Corona Immunitas, the COVID-19 Social Monitor and the Swiss MS Registry [16, 17]. Such a digital approach has the advantage of being independent from geography, thereby increasing the catchment area of interest [16, 17]. Participants from the Ukrainian population who are unable to fill out the questionnaires online are offered to complete the questionnaire through a phone interview (MAP-U only). As with the COVID-19 social monitor, results from MAP will be displayed in almost real-time on an online platform, providing the public, policymakers and scientists with the opportunity to monitor the prevalence and trajectories of symptoms of PTSD, depression, anxiety, and alcohol use disorder among the general population and by relevant subgroups.

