### Primary Endpoints

The primary endpoints are the prevalence and incidence of symptoms of PTSD, depression, anxiety, and alcohol use disorder. Since we will not be able to establish diagnoses through mental healthcare experts (psychiatrists or psychologists) according to the International Classification of Disease (ICD)- 10/11, or the Diagnostic and Statistical Manual of Mental Disorders (DSM)- 5, we rely on commonly used, standardized questionnaires which we selected following a systematic selection process [18]. For the four mental health conditions of interest, we identified potential instruments and compared them against our selection criteria: (a) should have strong psychometric properties (construct validity, internal consistency reliability, test-retest reliability, and ability to detect change over time) to capture symptoms; (b) estimates of sensitivity and specificity are available (c) can be implemented in digital surveillance (i.e., can be completed independently by participants); (d) are available in the Ukrainian language; (e) are appropriate in the context of the war in Ukraine; (f) have established cut-offs for the presence or likely presence of the four conditions of interest; (g) are or have been used in other population-based studies; (h) are short in duration or low burden to complete; (i) have been previously used in Ukraine. Instruments were discussed and final decisions made at an international working group meeting held in Zurich in Spring 2023.

Based on the criteria mentioned above, we selected the Posttraumatic Stress Disorder Checklist (PCL-5) for the assessment of PTSD, Patient Health Questionnaire (PHQ-9) for depression, generalized anxiety disorder 7 (GAD-7) for anxiety, and Alcohol Use Disorders Identification Test (AUDIT) for the alcohol use disorder. References for each of the instruments regarding the validation of psychometric properties (in a general non-Ukrainian population), the translation process into Ukrainian, and validation and/or utilisation in the Ukrainian population are provided in Table 1. Furthermore, the selected instruments are aligned with those used by the Global Burden of Disease (GBD) from The Institute for Health Metrics and Evaluation.

**TABLE 1 T1:** Mental Health Assessment of the Population, Switzerland, 2024

Instrument	Sensitivity %/Specificity % (score of instrument as cut-off)	Psychometric properties	Translation process	Validation/utilisation in Ukraine

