Participants from these oblasts will be selected by an age-stratified (18–24, 25–44, 45–64, and 65+ years of age) random sample based on a database provided to the Center for Social Research by the State Statistics Service of Ukraine.

Inclusion criteria for the random sampling: adults (aged ≥18 years) who are residents of the participating oblasts as specified above, providing informed consent and are able to complete the surveys (available in Ukrainian) online or by phone interview.

Excluded from the MAP-U study are individuals who cannot be reached on multiple attempts and those who are in military service and perform combat missions as part of the territorial defence, the armed forces of Ukraine or other military formations.

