#### MAP-Z

The target population of MAP-Z is adult Ukrainians who fled from Ukraine and currently live in the canton of Zurich. The source population is Ukrainians registered with refugee status S in the canton of Zurich and the study population consists of a random selection of this group of persons conducted by the Swiss Federal Statistical Office (FSO).

Inclusion criteria for the random, age-stratified (same age categories as for MAP-U) sampling are adults (aged ≥18 years) from Ukraine with refugee status S residing in the Canton of Zurich, providing informed consent and able to complete the surveys (available in Ukrainian) online. Exclusion criteria are individuals who cannot be reached on multiple attempts.

For the control group, adults from the general population of the Canton of Zurich will be randomly selected from the resident registry by the Swiss FSO, again age-stratified (same age categories as for MAP-U).

Inclusion criteria for the random sampling are adults (aged ≥18 years) residing in the Canton of Zurich with either Swiss citizenship or residence permit B or C, providing informed consent and able to complete the surveys (available in German) online.

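### Phone completion is open to people unable to respond online in MAP-U only, so Ukraine-versus-Zurich comparisons carry a mode and offline-coverage difference that the same-protocol statement does not acknowledge

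*Protocol article*

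**What the plan says.** All references are to the protocol article.

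- **Study Design, on comparability:** "To maximize comparability between MAP-U and MAP-Z, we will use the same mental health surveillance protocol".
- **Study Design, on completion:** people in the Ukrainian population who cannot complete the questionnaires online "are offered to complete the questionnaire through a phone interview (MAP-U only").
- **Study Design, on contact:** MAP-U starts with email, and "If there is no response, we will approach them via Telegram or phone calls". MAP-Z starts with postal mail.
- **Eligibility, MAP-U:** people qualify if they "are able to complete the surveys (available in Ukrainian) online or by phone interview".
- **Eligibility, MAP-Z refugees:** adults "with refugee status S residing in the Canton of Zurich, providing informed consent and able to complete the surveys (available in Ukrainian) online".
- **Eligibility, MAP-Z controls:** adults "providing informed consent and able to complete the surveys (available in German) online".
- **Primary Endpoints:** one selection criterion was that an instrument "can be implemented in digital surveillance (i.e., can be completed independently by participants"). One sensitivity and specificity pair is given per instrument, with no distinction by mode.
- **Statistical Methods:** the Bayesian prevalence model names age group and cluster of oblasts as adjustment variables. The association models are to adjust for potential confounders in general terms. Mode is named in neither.

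**The concern.** The article claims a common protocol and then fixes two different rules on who can take part and how. An adult who cannot respond online can be enrolled in Ukraine and cannot be enrolled in Zurich. Two differences follow.

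1. **Coverage.** By rule, MAP-U represents online and offline adults, while MAP-Z represents online-capable adults only. This holds whatever the effect of an interviewer.
2. **Measurement.** Some MAP-U answers on alcohol, trauma and mood are given to an interviewer. All MAP-Z answers are self-completed.

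A difference between Ukrainians in Ukraine and refugees in Zurich would then mix residence with mode and coverage. Objective 2 covers both groups, the abstract promises comparable data, and results are to be displayed in almost real time for policymakers. A reader of the same-protocol sentence would have no reason to suspect this component.

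**Working it through.** **Step 1. Set the rules side by side.**

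| Feature | MAP-U | MAP-Z refugees | MAP-Z controls |
|---|---|---|---|
| Instruments, cut-offs, 3-monthly schedule, age strata | shared | shared | shared |
| First contact | email, then Telegram or phone | post | post |
| Completion | online or phone | online | online |
| Person unable to respond online | eligible | not eligible | not eligible |

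The same-protocol statement holds for the first row and not for the others. Refugees and Zurich controls match on every row, so their contrast is free of this problem.

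**Step 2. Reproduce the plan's sizing figures.** Inputs from Sample Size Considerations and Calculation: prevalence 40%, precision ±5 points, attrition 15%.

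- n = 1.96² × 0.40 × 0.60 / 0.05² = 368.8, so 369, as stated.
- 369 / 0.85 gives 435, as stated.
- 12 strata × 435 = 5,220, as stated.

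**Step 3. Write the shift.** Let s be the phone share in MAP-U and d the phone-minus-online difference in screen-positive rate. The MAP-U rate is (1 − s) × online rate + s × phone rate = online rate + s × d. The whole-sample estimate therefore differs from the online-only estimate by s × d. Here d contains both the interviewer effect and the difference between the people reached, and it can have either sign.

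The article gives neither s nor d. Assuming |d| = 5 points:

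| s | Raw shift, s × d | After correction, PCL-5 (÷ 0.88) | After correction, AUDIT (÷ 0.50) |
|---|---|---|---|
| 5% | 0.25 | 0.28 | 0.5 |
| 20% | 1.0 | 1.14 | 2.0 |
| 50% | 2.5 | 2.84 | 5.0 |

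The divisors are sensitivity + specificity − 1: 0.94 + 0.94 − 1 = 0.88 and 0.65 + 0.85 − 1 = 0.50. The divisor assumes the same accuracy in both modes. With |d| = 10 points every entry doubles.

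**Step 4. Compare on one scale.** Correction divides the shift and the half-width by the same factor, so a corrected shift must be set against a corrected half-width.

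For AUDIT at the expected 15%, the apparent prevalence is 0.65 × 0.15 + 0.15 × 0.85 = 0.225, with variance term 0.225 × 0.775 = 0.1744. Treating accuracy as known and assuming simple random sampling:

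- One stratum, n = 369: raw 1.96 × √(0.1744/369) = 4.3 points; corrected 8.5.
- All MAP-U, n = 5,220 × 0.85 = 4,437: raw 1.2; corrected 2.5.
- MAP-U versus refugees, 4,437 v 1,030: raw 1.96 × √(0.1744 × (1/4,437 + 1/1,030)) = 2.8; corrected 5.7. The 1,030 is 1,212 × 0.85, with 1,212 = 2 × 435 + 2 × 171. The article's total of 1,220 would change little.

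Against the raw 2.8-point half-width of the overall contrast, shifts of 0.25, 1.0 and 2.5 points are 9%, 36% and 89% of it. The ratios are the same after correction (0.5, 2.0 and 5.0 against 5.7).

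**The case against.** **The statement is about maximizing comparability, not identity, and the phone exception is openly labelled.** This is fair as far as it goes: most of the protocol is shared, and the phone option improves coverage within Ukraine. But the exception appears in the eligibility criteria of all three groups, and the same-protocol sentence is not qualified.

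**No formal resident-versus-refugee test or war-effect estimand is specified.** This stands. The comparison is only implied, by the stated aim of comparability and by Objective 2. The point therefore applies to any such comparison that is made, not to a named analysis.

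**Handling of mode may be in a full protocol or SAP that is not shown.** This also stands, so the absence of a mode covariate or sensitivity analysis is not itself the point. The point is that the article states one protocol and sets two.

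**The direction is unknown.** A reader might infer that interviewers lower reporting, so that MAP-U prevalence is biased down, most of all at 65+ and unevenly across clusters. The documents support none of this. If offline people are more affected, coverage would push MAP-U prevalence up and could cancel or outweigh an interviewer effect.

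**The size is assumed.** This stands. Phone completion is reserved for people unable to go online, and nothing in the article supports a share as high as 50%.

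**The selection criterion on independent completion is not breached.** This is correct: it asks that instruments can be self-completed and does not rule out an interviewer as fallback.

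**Conclusion.** The contradiction is established from the text. The same-protocol statement does not hold for mode of completion, eligibility of people unable to respond online, or contact route. Any MAP-U versus MAP-Z comparison made as written therefore carries a mode and coverage component.

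Its sign and size are unknown. On an assumed 5-point phone-online difference, it is about a tenth of the overall AUDIT half-width at a 5% phone share and close to the whole of it at 50%. It does not shrink as the sample grows.

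Two stronger readings should be resisted. The first is that the misclassification correction makes the problem worse relative to precision. It does not, because it scales shift and half-width alike; setting a corrected AUDIT shift against the plan's ±5 mixes scales, since the corrected stratum half-width is about 8.5. The second is that the comparability of the whole programme fails. The shared elements stand, and so does the refugee-versus-control contrast.

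**What to change.** 1. Record completion mode for every participant at every wave.
2. Beside every MAP-U versus MAP-Z comparison, report the result restricted to MAP-U online completers, which is the population that MAP-Z can enrol. The gap between the two results is the s × d of the working, so the problem becomes measurable.
3. Keep phone respondents in Ukraine-only prevalence, and add an online-only sensitivity analysis for cluster, age and trend results.
4. Qualify the same-protocol sentence in Study Design to name the difference in completion mode and eligibility.

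Do not add mode as a routine covariate. Phone is offered only to people unable to respond online, so mode is confounded with being offline, and adjustment could remove genuine differences.

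**Cost:** one data field and some analysis wording. The online-only comparison is somewhat less precise. With 20% by phone, MAP-U falls from 4,437 to 3,550, and the overall half-width grows by √[(1/3,550 + 1/1,030)/(1/4,437 + 1/1,030)] = 1.02. With 50% by phone (2,219 remaining) the factor is 1.09. The loss is likely to be larger at 65+, if phone use is concentrated there. The restricted result applies only to online-capable people. It leaves the difference in contact route in place.
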